### 7.1.6 Withdrawal and replacement of subjects

#### Criteria for withdrawal

Subjects may prematurely discontinue from the study at any time. Premature discontinuation from the study means that the subject did not undergo an end of study examination as planned per protocol.

Subjects must be withdrawn under the following circumstances:

- at their own request
- if the Investigator feels it would not be in the best interest of the subject to continue
- if the subject violates conditions laid out in the consent form / information sheet or disregards instructions by the study personal

In all cases, the reason why subjects are withdrawn must be recorded in detail in the CRF and in the subject's medical records. Should the study be discontinued prematurely, all study materials (completed, partially completed and empty CRFs) will be retained.

#### Follow-up of patients withdrawn from the study

In case of premature discontinuation after study drug intake, the investigations scheduled for the EOS visit will be performed on day 29 after study entry. Day 60-day and 90-day mortality will be assessed, either by telephone visit, mortality register or by chart review (in case of hospitalization). The subjects will be advised that participation in these investigations is voluntary. Furthermore, they may request that from the time point of withdrawal no more data will be recorded and that all biological samples collected in the course of the study will be destroyed.

#### Replacement policy

Only patients who discontinue the trial before intake of any trial drugs will be replaced. Patients who received at least one dose of the respective treatment will not be replaced, due to the limited availability of trial drugs.

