| PATIENTS / GROUPS           | 
For the main “antiviral therapy” study currently 4 treatment arms are planned. Treatment arm 4 refers to standard of care (SOC) and will be the “control arm” of the study. A preliminary sample size calculation has been performed for the comparison of two groups based on a recent publication.
 
Therefore, we plan for n=100 patients per treatment arm in the main study. This number may increase after the interim analysis. This means that currently the main study is planned for approximately N=500 patients.
 
After inclusion of 20 and 50 patients per arm, interim analyses will be performed to draw conclusions on the sample size and to stop trial arms for safety or futility.
 
An even randomization ratio for “antiviral” arms (1:1:1:1) is theoretically intended but a dynamic assignment will occur according to available and permissible treatments (i.e. where no absolute contra-indication exists).
 |             |                             |             |                            |             |

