## 8.2 Randomization and stratification

This is a randomized trial with different active treatments. However, for this platform trial, some special circumstances need to be considered. In the “Main” antiviral study three treatment options remain active within the randomized trial. Sub-study A, B, C, will also be conducted as randomized trials against standard of care. Randomization will be carried out online by [www.meduniwien.ac.at/randomizer](http://www.meduniwien.ac.at/randomizer). No stratification will be applied, except for the asunercept part of the trial. Based on the currently known risk factors, hospitalized patients are probably older and have more comorbidities, compared to a “general population”. Moreover, the sample sizes are relatively small, which precludes further stratification due to statistical reasons.

For sub-study B randomization will occur within the treatment group. In this cohort (labelled as “sub-study B”), patients with established arterial hypertension (and treatment) may be switched and patients with blood pressure  $\geq 130/85$  mmHg will be randomized to new treatments. Importantly, those patients with blood pressure  $\geq 130/85$  mmHg but  $< 140/90$  mmHg, who are randomized to non-RAS blocking treatment will not receive any treatment. Patients will be randomized to the following two treatment options using an allocation ratio of 1:1

- RAS blocker containing treatment (candesartan)
- Non-RAS blocker containing treatment (e.g. nitrendipin/amlodipin/doxazosin)

Thus, clinicians may decide within the first 24 hours if patients who participate in the main antiviral study A will also fulfill the criteria for one of the sub-studies. It is currently not intended to simultaneously enroll a patient in sub-studies A or B. Within sub-studies randomization will be done using the same software.

For sub-study C:

Asunercept: a 3:1 randomization against standard of care will be done, whereas three different doses of asunercept will be tested. Stratification according to the WHO scale at screening will be performed (only WHO scales 4, 5, and 6 are available for inclusion (patients with oxygen demand).

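### Section 7.1.6 ties replacement and day-29 follow-up after withdrawal to trial-drug intake, so both rules are undefined or asymmetric for controls who take no trial drug

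*Protocol*

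**What the plan says.** Section 7.1.6 of the protocol has a two-sentence replacement policy: "Only patients who discontinue the trial before intake of any trial drugs will be replaced", and "Patients who received at least one dose of the respective treatment will not be replaced, due to the limited availability of trial drugs".

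The paragraph before it covers follow-up after withdrawal. It opens: "In case of premature discontinuation after study drug intake, the investigations scheduled for the EOS visit will be performed on day 29 after study entry". The next sentence provides for 60-day and 90-day mortality by telephone, register or chart review, with no drug-intake condition of its own. It then adds: "The subjects will be advised that participation in these investigations is voluntary".

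The synopsis makes arm 4 the standard-of-care (SOC) control of the main study. Section 11 gives each part of the platform its own SOC control. Sections 8.1 and 8.1.1 list no agent or dose for arm 4 or for the sub-study C controls. In section 8.2, sub-study B patients at or above 130/85 mmHg but below 140/90 mmHg "who are randomized to non-RAS blocking treatment will not receive any treatment".

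**The concern.** Both rules need an event, drug intake, that many controls never have. Neither names randomisation or any other starting point that exists in every arm.

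Sites apply these rules while the trial is running. If they apply them literally, whether a patient is replaced and whether day-29 status is sought after withdrawal will depend on the allocated arm. Section 8.3 makes the trial open label, so the reasons for leaving can also differ by arm. An analysis plan cannot recover outcomes that nobody collected. The reason given for not replacing dosed patients, scarce drug supply, does not apply to SOC.

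**Working it through.** **1. The plan's own figure.** Section 11.2 states 83.15% power with 154 events, hazard ratio 1.6 and two-sided alpha 0.05. The Schoenfeld approximation gives Φ(ln 1.6 × √(154/4) − 1.96) = Φ(0.470 × 6.205 − 1.96) = Φ(0.956) = 83.05%. The figure reproduces, so the sample size is not in dispute. Section 11.2 gives no dropout rate.

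**2. Section 7.1.6 applied literally to a patient who withdraws on day 12.**

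| Patient | Replaced? | Day-29 investigations after withdrawal? |
|---|---|---|
| Drug arm, at least one dose | No | Offered, voluntary |
| Drug arm, never dosed | Yes | Not triggered |
| Control, no trial drug at all | Yes | Not triggered |
| Main-study SOC patient taking a sub-study drug | No | Offered, voluntary |

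The third row applies on any day, because such a patient is always before first intake.

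**3. The other sections.** Section 7.1.5 has the clinical status of all patients evaluated on day 29. Section 8.5.4 assesses day-60 and day-90 mortality without mentioning drug intake. These general statements and the first follow-up sentence of 7.1.6 cannot all be applied to a withdrawn control.

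**4. The link to the analysis.** Replacement alone adds a randomised patient and does not bias the comparison. Bias needs the original patient to leave the analysis. Section 11.1 defines the modified ITT set by randomisation plus, in brackets, at least one dose of study drug. Taken literally, that would exclude every control without a study drug, which cannot be meant. Some other reading must be applied to controls, and the protocol does not say whether it keeps a replaced control.

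**5. Illustration only.** Assumptions:
- dropout d is the same in both arms, and the drug has no effect;
- drug-arm dropouts stay in the analysis, while SOC dropouts are replaced and removed;
- the improvement rate is 0.043 per day, which is section 11.2's figure for a 16-day median assumed for lopinavir/ritonavir, not for SOC.

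Improved by day 29 among those who stay: 1 − exp(−0.043 × 29) = 71.3%. To keep 100 SOC patients, 100/(1 − d) must be randomised. If dropouts never improve, the drug arm shows (1 − d) × 71.3%. If all of them improve, it shows d + (1 − d) × 71.3%.

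| d (assumed) | Randomised to SOC | False gap, dropouts never improve | False gap, dropouts all improve |
|---|---|---|---|
| 5% | 105 | 3.6 points against the drug | 1.4 points for the drug |
| 10% | 111 | 7.1 points against | 2.9 points for |
| 20% | 125 | 14.3 points against | 5.7 points for |

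These are extremes on a day-29 proportion, whereas the primary test is a log-rank test. On an event-rate scale, 100 patients at 0.043 per day contribute about 1,657 patient-days by day 29. If 10 non-improvers leave on day 12, that falls by 10 × 17 to 1,487. Deleting them instead of censoring them removes a further 10 × 12, leaving 1,367. The SOC rate moves from 71.3/1,487 = 0.048 to 71.3/1,367 = 0.052, a ratio of 1.09. On the log scale this is ln 1.09 / ln 1.6, about 18% of the planned effect.

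**6. Where it would matter.** The synopsis says arm 4 will be analysed only descriptively, although it also plans comparison of the antiviral arms with SOC. In sub-study C, SOC is the comparator: section 7.1.1 plans 100 asunercept controls and 20 Pentaglobin controls. Two replaced Pentaglobin controls would be 2/20 = 10% of that arm.

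**The case against.** The best defence is that the text is ambiguous rather than demonstrably one-sided. The second replacement sentence refers to the respective treatment. The synopsis lists SOC as arm 4 under investigational drug, and section 7 allows SOC to include remdesivir. On that reading an SOC patient could count as treated. This stands as a possible reading, but it leaves a dose of SOC undefined and does not fit the untreated sub-study B controls. Section 7 and the sub-study C list in 11.6.2 also leave room for a placebo, which would supply a first dose. However, section 8.1 lists none and 8.3 declares the trial open label.

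Several limits on the point stand in full:
- A reader might infer that a withdrawn control is owed no follow-up at day 29, 60 or 90. The text does not support this. The day-60/90 mortality sentence has no intake condition, section 8.5.4 is general, and section 7.1.5 covers all patients on day 29. Follow-up is voluntary for drug-arm patients too.
- Early discharge is not withdrawal: section 8.5.3 has discharged patients telephoned on days 11 and 29.
- Later recruitment of replacement controls is partly handled by the calendar-time adjustment in the additional Cox model of section 11.6.1.
- Section 7.1.6 does not say that a newcomer fills the vacated arm.

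**Conclusion.** The point holds in limited form. For controls who take no trial drug, the replacement rule and the day-29 rule after withdrawal are undefined or, read literally, differ from those for dosed patients. The day-29 rule also conflicts with section 7.1.5.

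It would go too far to conclude that replacement by itself breaks the randomised comparison, or that a planned main-study contrast with SOC is damaged by a known amount. The first requires the original patient to leave the analysis, which the dose wording in section 11.1 makes possible but does not state. For the second, the protocol plans only a descriptive analysis of arm 4 and gives no SOC improvement rate.

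The size cannot be estimated without a dropout rate. The illustrative gaps, from 14.3 points against the drug to 5.7 points in its favour, rest on assumed dropout of 5% to 20%, extreme outcomes for those who leave, and removal of replaced controls. The exposure is mainly in the sub-study C comparisons with SOC.

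**What to change.** - **Follow-up after withdrawal (7.1.6):** make the condition withdrawal after randomisation instead of after drug intake. Day-29 status is then sought for every withdrawn patient, in any arm, who does not refuse.
- **Replacement policy (7.1.6):** either replace nobody, or use one trigger counted from randomisation that is the same in all arms including SOC. Make any replacement a new randomisation, and keep the original randomised patient in the primary analysis.
- **Reconcile** sections 7.1.5, 8.5.4 and 11.1 with the new wording. In 11.1, say how the at-least-one-dose condition applies to controls with no study drug.

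The cost is a few sentences of protocol text, some extra telephone or register checks, and possibly slightly fewer SOC patients than under open-ended replacement. Other common triggers would serve equally well, provided every arm has the same one.

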### 7.1.7 Premature termination of the study

The sponsor has the right to close this study at any time. The IEC and the competent regulatory authority must be informed within 15 days of early termination.

The trial or single dose steps will be terminated prematurely in the following cases by the local PI:

- If adverse events occur which are so serious that the risk-benefit ratio is not acceptable.
- If the number of dropouts is so high that proper completion of the trial cannot realistically be expected.
- If futility of treatment is proven (e.g. relevant publication by other groups)

## 8 METHODOLOGY

### 8.1 Study medication

**Treatment Arm 1 (INACTIVE):**

Active agent and characteristics: Hydroxychloroquine

Trade name of the agent: Quensyl

Manufacturer: Sanofi Aventis

Drug supply: central pharmacy of each trial center

Storage Instructions: room temperature

Route of administration: p.o.

**Treatment Arm 2:**

Active agent and characteristics: Lopinavir/Ritonavir

Trade name of the agent: Kaletra

Manufacturer: AbbVie

Drug supply: central pharmacy of each trial center

Storage Instructions: room temperature

Route of administration: p.o.

**Treatment Arm 3:**

Active agent and characteristics: remdesivir

Trade name of the agent: Veklury

Manufacturer: Gilead Sciences

Drug supply: central pharmacy of each trial center

Storage Instructions: refrigerator (2-8 degrees Celsius)

Route of administration: i.v.

**Sub-study A:**

Active agent and characteristics: rivaroxaban

Trade name of the agent: Xarelto

Manufacturer: Bayer AG

Drug Supply: central pharmacy of each trial center

Storage instructions: room temperature

Route of administration: p.o.

**Sub-study B:**

Active agents and characteristics: candesartan

Trade names of the agents: Blopress

Manufacturer: Takeda Pharma

Drug supply: central pharmacy of each trial center

Storage Instructions: room temperature

Route of administration: p.o.

**Sub-Study C:**

Active agent and characteristics: Asunercept

Trade name of the agent: None

Manufacturer: Nuvisan GmbH

Drug supply: central pharmacy of each trial center

Storage Instructions: refrigerated at 2-8 °C until use

Route of administration: i.v.

Active agent and characteristics: Immunoglobulin

Trade name of the agent: Pentaglobin®

Manufacturer: BIOTEST PHARMA GMBH

Drug supply: central pharmacy of each trial center

Storage Instructions: refrigerated at 2-8 °C until use

Route of administration: continuous iv infusion

### 8.1.1 Dosage and administration

#### „ANTIVIRAL“ THERAPIES

**Treatment Arm 1: Hydroxychloroquine (INACTIVE)**

Initial dose: 200mg 2-0-2

Maintenance dose: 200mg 1-0-1

Route of administration: p.o.

Duration: minimum of 7 Days but at least until sustained improvement

**Treatment Arm 2: Lopinavir/Ritonavir**

Initial dose: 200mg/50mg 4-0-4

Maintenance dose: 200mg/50mg 3-0-3

Route of administration: p.o.

Duration: minimum of 7 Days but at least until sustained improvement

**Treatment Arm 3: Remdesivir**

Initial dose: 200mg/day

Maintenance dose: 100mg/day

Route of administration: i.v.

Duration: minimum of 5 days in total

#### „ADJUNCTIVE“ THERAPIES

**Sub-Study A: Rivaroxaban**

Initial dose: 10 mg 1/2-0-1/2 (10 mg was non-inferior to 40 mg enoxaparin in acutely ill patients (75); the split dose is provided to minimize peak levels and to obtain smaller peak/trough ratios)

Maintenance dose: down-titration allowed in case of high anti-FXa activity before the next dose

Route of administration: p.o.

Duration: during hospitalization, unless discontinuation is necessary for clinical reasons

#### **Sub-Study B: RAS blockade**

Initial dose: candesartan 8 mg 1-0-0; (compared to standard of care, e.g. nitrendipin 10 mg 1-0-1, amlodipine 5mg 1-0-0 or doxazosin 2 mg 1-0-1)

Maintenance dose: Uptitration to normotension

Route of administration: p.o.

Duration: Through recovery, unless discontinuation is necessary for clinical reasons

#### **Sub-Study C:**

Asunercept

Initial dose: 25 mg, 100 mg or 400 mg

Maintenance dose: same as first dosage, unless other specified by DSMB or interim analysis.

Route of administration: i.v. (in 200 mL NaCl (0.9%))

Duration: up to 4 weeks, treatment will cease when patient can be discharged from hospital (because of significant amelioration) or when patient has deceased.

25mg infusion solution:

For preparation of the infusion solution, 1.25 mL Asunercept (corresponding to 25 mg) is taken from the vial with a syringe and is diluted into the infusion solution. The preparation of the final Asunercept solution for infusion should be performed at room temperature (if possible under aseptic conditions, e.g., laminar flow hood)

100mg infusion solution:

For preparation of the infusion solution, 5mL Asunercept (corresponding to 100 mg) is taken from the vial with a syringe and is diluted into the infusion solution. The preparation of the final Asunercept solution for infusion should be performed at room temperature (if possible under aseptic conditions, e.g., laminar flow hood).

400mg infusion solution:

For preparation of the infusion solution, the complete content of two Asunercept vials (corresponding to 400 mg) is taken with a syringe and is diluted into the infusion solution. The preparation of the final Asunercept solution for infusion should be performed at room temperature (if possible under aseptic conditions, e.g., laminar flow hood).

The total amount of the infusion solution will be approx. 201 – 270 mL depending on the size of the NaCl solution container and the dose of Asunercept.

The IMP solution ready for infusion should be kept at room temperature, and must be applied to the patient within 3 h after preparation (including infusion time).

Asunercept will be administered once per week as an approx. 30 min i.v. infusion in a total volume of approx. 201 – 270 mL and using a commercial 0.2 µm in-line-filter (0.22 µm nominal pore size).

If the weight of a patient is below 50 kg and 400 mg per dose are applied, the infusion time needs to be increased and Asunercept must be administered as an approx. 45 min i.v. infusion.

For safety reasons, patients will be closely monitored throughout infusion. In case of an allergy or incompatibility reaction during infusion, infusion should be stopped and the event must be documented in the CRF.

For Pentaglobin:

dose: continuous IV application of a total dose of 7ml/kg/day

Route of administration: continuous iv infusion over 12h

Duration: 5 days

### 8.1.2 Study-drug up- and down titration

**Sub-study A:** Down titration is allowed in case of excessive anti-FXa activity

**Sub-study B:** Up/down titration of antihypertensive medication until normotension is planned.

**Sub-study C: Asunercept:** in case of efficacy or safety signals during the interim analyses, treatment arms may be closed and patients still treated with Asunercept may be switched to the safe or effective higher or lower dose.

#### **Dose modification for individual patients**

Dose of Asunercept in individual patients may be considered in the event of:

1. In case signs of intolerability or toxicity signs are detected by the clinician. In such case, Asunercept dose may be reduced to the next lower dose group.
2. In case differences in efficacy are seen at interim analyses, patients will be switched from the less effective dose(s) to the more effective dose(s) or to equally effective lower dose(s).

### 8.1.3 Study drug interruption or discontinuation

The Investigator must temporarily interrupt or permanently discontinue the study drug if continued administration of the study drug is believed to be contrary to the best interests of the patient.

The interruption or premature discontinuation of study drug might be triggered by an AE, a diagnostic or therapeutic procedure, an abnormal assessment (e.g., laboratory abnormalities), or for administrative reasons, in particular withdrawal of the patient's consent.

The reason for study drug interruption or premature permanent discontinuation must be documented in the CRF.

### 8.1.4 Study drug premature permanent discontinuation

#### **Study drug premature permanent discontinuation due to an adverse event**

If the reason for premature permanent discontinuation of study treatment is an AE, the patient should have a "Premature End of Study (EOS)" visit with all the assessments performed before the study drug discontinuation, whenever possible.

**Study drug premature permanent discontinuation due to another reason than adverse event**

If the reason for premature permanent discontinuation of study treatment is not an AE, the patient should be withdrawn from the study (withdrawal of consent) and have the end of study (EOS) visit with all the assessments performed before the study drug discontinuation, whenever possible.

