### 7.1.5 Study duration

The clinical status of all patients will be evaluated on day 29. Thereafter, the trial ends for the individual patient randomized to antiviral treatment arms. The study ends after full recovery (or death) for patients in sub-studies B and C.

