#### Pharmacokinetic properties

Human immunoglobulin is immediately and completely bioavailable in the recipient's bloodstream after intravenous administration. It is distributed relatively quickly between the plasma and the extravascular fluid. After about 3-5 days, a balance is reached between the intra- and extravascular compartment.

The half-life of the immunoglobulins contained in Pentaglobin is comparable to the body's own immunoglobulins. This half-life can vary from patient to patient, especially in primary immunodeficiency syndromes.

In conclusion, we believe that the risks for most of the patients, based on side-effect profile of the individual treatments, are acceptable and the benefits, especially in the light of a lack of standard treatment and also with a focus on the upcoming challenges of the healthcare system, are remarkable, for the individual patients, as well as for the large number of expected SARS-CoV-2 patients worldwide.

**General Update Amendment:** Although, the estimates for COVID-19 associated mortality expectedly decreased (mainly due to a different testing strategy) and although, dexamethasone and remdesivir have partially shown beneficial effects in COVID-19 patients, there is still massive pressure on health systems globally. There is still a requirement for more effective therapies that may help to prevent intensive care unit admission and that may accelerate recovery in hospitalized patients. Currently, in numerous countries the numbers of patients with COVID-19 are rising and shortages in hospital and ICU beds are expectable. Asunercept not only holds the potential to beneficially impact on COVID-19, but may also be effective in other virus-induced acute respiratory distress syndrome. The clinical value of remdesivir is currently illdefined. Therefore, in hospitals and in situations where remdesivir is not part of SOC, patients may be randomized to receive remdesivir, SOC or lopinavir/ritonavir. However, since remdesivir is the only approved drug for COVID-19 patients in other arms may still receive remdesivir, if the clinical situation requires it. This decision will lie in the hand of treating physicians.

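### Section 8.1.4 ties stopping study drug to leaving the study; this contradicts the follow-up promised elsewhere and, if followed, cuts off the daily scores behind the primary endpoint

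*Protocol*

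**What the plan says.** Section 8.1.4 has two branches. For a stop not due to an adverse event, "the patient should be withdrawn from the study (withdrawal of consent) and have the end of study (EOS) visit". For the other branch, "If the reason for premature permanent discontinuation of study treatment is an AE, the patient should have a" premature end-of-study visit. In both, the assessments are to be done before the drug is discontinued, where possible.

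Section 8.1.3 shows that the non-adverse-event branch is wider than withdrawn consent. Besides adverse events and diagnostic or therapeutic procedures, it names "an abnormal assessment (e.g., laboratory abnormalities), or for administrative reasons", and singles out withdrawn consent as one case.

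Other sections say something different:

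- Section 7.1.6, on criteria for withdrawal: "Subjects must be withdrawn under the following circumstances". The list is the subject's own request, the investigator's view of the subject's interest, and breach of consent conditions or instructions. Stopping study drug is not on it.
- Section 7.1.6, on follow-up: after premature discontinuation following drug intake, "the investigations scheduled for the EOS visit will be performed on day 29 after study entry", and day-60 and day-90 mortality are also assessed.
- Section 7.1.5: "The clinical status of all patients will be evaluated on day 29".
- Section 8.5.3: the WHO scale and other clinical endpoints are obtained every day in all patients.
- Section 11.6.1: the score is taken daily in hospital to day 29, or on days 11 and 29 after discharge. The event is an improvement of at least one category, held on two successive days, relative to randomization.
- Section 11.5: missing data are not imputed.

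**The concern.** The two sets of instructions cannot both be followed. Under 8.1.4, a patient whose drug is stopped for an abnormal laboratory value or an administrative reason leaves the study and has the final visit then. Under 7.1.5, 7.1.6, 8.5.3 and 11.6.1 the same patient is still scored.

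The primary endpoint depends on a daily series. If scoring ends at drug stop, the patient is censored there. One contact on day 29 can show that a patient is better, but cannot date the first of two consecutive improved days.

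The route is also unequal between arms. Section 8.1 lists no study drug for the standard-of-care arm, so the rule cannot trigger there. In a comparison of drug with standard of care (main study, and sub-study C against standard of care), this loss falls on one side only. If the patients who stop differ in prognosis, the primary analysis, meant to follow a modified intention-to-treat set, is biased.

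**Working it through.** **1. The plan's own figure.** Section 11.2 gives 100 per group, 154 events, hazards 0.069 and 0.043 per day (HR 1.6), two-sided alpha 0.05 and power 83.15%. Schoenfeld's formula gives power = Φ(√154/2 × ln 1.6 − 1.96) = Φ(6.205 × 0.470 − 1.96) = Φ(0.956) = 83.05%. The figure is reproduced.

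**2. What follow-up do 154 events assume?** Expected events by day t with nobody lost are 100(1 − e^(−0.069t)) + 100(1 − e^(−0.043t)).

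- Day 27: 84.5 + 68.7 = 153.2
- Day 28: 85.5 + 70.0 = 155.5

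So 154 events correspond to complete follow-up to about day 27-28. The calculation leaves no allowance for patients lost after drug stop.

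**3. Loss unrelated to outcome, drug arm only.** The protocol states no discontinuation rate, so a range is used. Spread a loss fraction d over 28 days at rate g = −ln(1 − d)/28. Drug-arm events are then 100 × 0.069/(0.069 + g) × (1 − e^(−28(0.069 + g))).

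- d = 20%: g = 0.0080; 79.3 + 70.0 = 149.3 events; power 81.9%
- d = 30%: g = 0.0127; 75.9 + 70.0 = 145.9 events; power 81.0%

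If the loss falls early, on days 1-7, it costs more. By simulation, power goes from about 83-85% without loss to about 78-81% at 20-30%.

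**4. Loss related to outcome, no true effect.** Assume a fraction p of patients in both arms improves at half the usual rate, and that these patients are censored on days 1-7 in the drug arm only. After the first week the drug arm holds only usual-rate patients, while the control arm starts from an average rate of (1 − p/2) times usual. A rough hazard ratio is therefore 1/(1 − p/2). Log-rank simulation (100 per arm, 28 days; ranges are from repeated runs) agrees:

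| Loss p | 1/(1 − p/2) | Simulated HR | Type I error |
|---|---|---|---|
| 5% | 1.03 | about 1.03 | about 6% |
| 10% | 1.05 | about 1.06 | about 6% |
| 20% | 1.11 | about 1.11 | 8-10% |
| 30% | 1.18 | about 1.17 | 12-13% |

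**5. Sensitivity to who stops.** These runs use a stronger selection: those lost on days 1-7 are drawn from the half of the drug arm with the longer, or the shorter, actual improvement times.

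- Slower half, no true effect: HR 1.05, 1.08 and 1.19 at 5, 10 and 20% loss, with type I error 5.6, 6.5 and 15.5%. The Monte Carlo error is about 0.5 points near 5%.
- Faster half, 20% loss: null HR 0.84, and power under the planned HR of 1.6 falls to about 61%.

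If the half-rate patients exist only in the drug arm, with no counterpart in control, the arms already differ before anyone is lost. The result is then an HR of about 0.97 with near-nominal error. The table in step 4 depends on the subgroup being equal in both arms.

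**The case against.** The strongest reply is that most of the remedy is already in the protocol. Sections 7.1.5, 7.1.6, 8.5.3 and 11.6.1 keep patients under observation and make no exception for stopped drug, so a site could reasonably go on scoring. That stands as far as it goes: loss of scores is what happens if 8.1.4 is followed, not what the protocol as a whole prescribes. It does not remove the conflict, because 8.1.4 is the section a site would consult when a drug is stopped.

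Several stronger readings are tempting, and the documents do not support them:

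- *Every drug stop means withdrawal.* This is explicit only for stops not due to adverse events. For adverse-event stops it is implied by the visit's name.
- *The case report form will record false consent withdrawals.* Section 8.1.4 sets no coding rule, and sections 7.1.6 and 8.1.3 require the actual reason to be documented. The parenthesis might even be meant to narrow the rule to withdrawn consent, but the stated condition is any reason other than an adverse event.
- *Deteriorating patients come off their assigned drug.* Section 8.4 says "patients in other arms may still receive remdesivir, if the clinical situation requires it", which does not say that the assigned drug stops, and section 8.1.10 leaves concomitant treatment to the physician. A link with prognosis is plausible: section 8.1.1 continues lopinavir/ritonavir at least until sustained improvement, and section 8.1.3 allows stops for abnormal assessments. It is not established.
- *Only drug arms lose patients.* The section 7.1.6 reasons can remove a patient from any arm.
- *The drug will look better.* Step 5 shows that the direction depends on who stops.

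The synopsis also says that arm 4, the standard-of-care arm, will be analyzed only descriptively, although elsewhere it calls that arm the control. Where two drug arms are compared, both face the same rule. The one-sided loss therefore concerns comparisons with standard of care.

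**Conclusion.** The contradiction is real and sits in operative text. Section 8.1.4 withdraws patients whom 7.1.6 does not list for withdrawal, and it places the final visit at drug stop where 7.1.6 places it on day 29. If it is followed, the series needed for the primary endpoint is cut short by a route that does not exist for standard-of-care patients.

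The size cannot be derived from the protocol. Under the equal-subgroup assumption the bias is small at 5-10% loss and material at 20-30%. Those higher rates are a lot to expect from the branch where withdrawal is explicit. Under outcome-unrelated loss the only cost is a few points of power. This should be fixed, but it does not by itself invalidate the design. It belongs in the protocol, because no analysis rule can recover scores that were never collected.

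**What to change.** Reconcile 8.1.4 with 7.1.5, 7.1.6, 8.5.3 and 11.6.1 by separating two things: stopping study drug, and leaving the study. Suggested content for 8.1.4:

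- A patient who stops study drug for any reason stays in follow-up: WHO scale daily while in hospital, the day-11 and day-29 contacts after discharge, and vital status at days 60 and 90.
- Data collection ends early only if the patient withdraws consent to follow-up or meets a withdrawal reason in 7.1.6.
- Withdrawal of consent is recorded only when it occurred. The reason for stopping drug is recorded separately.

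No change to when treatment is stopped is proposed.

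The cost is one paragraph and a case report form completion note. The patients concerned are mostly inpatients whose daily scores the protocol already requires.
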